### Data Collection From Participants

#### Data From Routinely Conducted Assessments and Clinical Records

Demographic data and height will be recorded at week –3 to –2. Blood tests (cholesterol and glycated hemoglobin), medication, body mass, vital parameters, and incremental cycle ergometry will be recorded 3 times (at week –3 to –2, time point 0, and week 10). Adverse event reporting will take place at week 10.

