## Methods

### Aim

The primary aim of this study is to pilot and assess the feasibility of a future randomized controlled trial design that will investigate the effectiveness of the aktivplan digital health intervention. In addition, the study will evaluate the usability, user experience, and acceptance of the aktivplan app, providing information on potential improvements.

The secondary aim of this study is to collect clinical outcomes to inform the sample size calculation for a future definitive effectiveness trial and to demonstrate the patient safety of the intervention.

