### Study Design

This is a multicenter, mixed method, randomized controlled pilot study. Forty patients undergoing phase II rehabilitation will be recruited from 2 study sites (20 patients per site). Study participants will be individually randomized to the intervention group (aktivplan digital health intervention) or control (standard care, ie, not including any routinely provided digital technologies) and will be followed up for 10 weeks after discharge from phase II rehabilitation.

The reporting of this study protocol adheres to the SPIRIT (Standard Protocol Items: Recommendations for Interventional Trials) statement [21], the CONSORT (Consolidated Standards of Reporting Trials) statement extension to randomized pilot and feasibility trials [22], and the TIDieR (Template for Intervention Description and Replication) checklist [23]. The SPIRIT, CONSORT, and TIDieR checklists are provided as Multimedia Appendices 1-3.

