Study procedures.Screening for eligibility: all patients admitted to phase II rehabilitation programs at the study sites are screened against study eligibility criteria.Recruitment: all eligible patients are invited to take part in the study. Consent is obtained from those who express interest to participate.Baseline data collection (weeks −3 to −2): baseline data are collected. A detailed description of measures is provided subsequently and in Figure 2.Randomization: patients are randomly allocated to the intervention or control group. Random allocation is concealed and stratified according to study site, patient sex, and patient exercise capacity.aktivplan physical activity planning session (week −1): participants allocated to the intervention group receive the aktivplan physical activity planning session before discharge from the phase II rehabilitation program.Data collection at discharge from phase II rehabilitation (time point 0): data are collected at discharge from phase II rehabilitation. A detailed description of measures is provided subsequently and in Figure 2.Follow-up period: patients in both study groups are followed up for 10 weeks after discharge from phase II rehabilitation. Patients in the intervention group use the aktivplan digital health intervention.Physical activity and heart rate measurements (week 8-10): patients in both study groups receive wearable sensor devices (accelerometer and heart rate sensor) for continuous measurement during waking hours for 3 weeks (weeks 8-10 of the follow-up period). A detailed description of measurements is provided subsequently.10-week follow-up (week 10): Data are collected in the concluding study visit. A detailed description of measures is provided subsequently and in Figure 2.aktivplan digital intervention for patients in the control group: Following completion of the study, patients in the control group are offered to receive the aktivplan physical activity planning session and use the aktivplan app for 2 weeks. No study data collection will be conducted during this period.

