### Outcomes

The primary outcomes address the primary study aim, that is, to pilot and assess the feasibility of a future randomized controlled trial design to investigate the effectiveness of the aktivplan digital health intervention; and to assess the usability, user experience, and acceptance of the aktivplan app. The primary outcomes are presented in Textbox 3.

The secondary outcomes address the secondary study aim, that is, the collection of clinical outcomes to inform the sample size calculation for a future definitive effectiveness trial and to provide evidence toward demonstrating patient safety of the intervention. The secondary outcomes are presented in Textbox 4.

Primary outcomes.Recruitment rate (number of recruits per week, percentage of screened patients who were recruited, and percentage of eligible patients who were recruited)Drop-out rate (number of drop-outs at the 10-week follow-up and percentage of recruited patients who dropped out)Data completeness (percentage of missing data fields in study database)Adherence to the aktivplan digital health intervention (automated use logging of the aktivplan app and video recording of the aktivplan physical activity planning session)Usability of the aktivplan app (mHealth App Usability Questionnaire)User experience of the aktivplan app (AttrakDiff mini questionnaire)User acceptance of the aktivplan app (Mobile App Rating Scale and Unified Theory of Acceptance and Use of Technology 2)Technical reliability of the aktivplan app (number and types of technical problems and qualitative data)Use of alternative and additional strategies for supporting physical activity (number and types of additional strategies and qualitative data)Experiences and perspectives of rehabilitation professionals regarding the intervention and study procedures (qualitative data from focus groups)

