Secondary outcomes.Exercise capacity (highest mechanical power output achieved during incremental cycle ergometry, peak power)Physical activity behavior (accelerometry and daily minutes of moderate to vigorous physical activity)Body massArterial blood pressureBlood cholesterol levelsGlycated hemoglobin levelsSmoking (number and type of smoking products per week)Health-related quality of life (EQ-5D-5L questionnaire)Exercise self-efficacy (Exercise Self-Efficacy Scale)Depression and anxiety (Patient Health Questionnaire-4)Kinesiophobia (selected items from the Tampa Scale of Kinesiophobia)Patient safety (adverse events reporting according to regulatory standards: number, type, and severity of adverse events)

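### Adverse event reporting is fixed at week 10 only, so events in participants who withdraw from the study may be missed, and the aim to demonstrate safety exceeds what about 20 exposed patients can show

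*Protocol article*

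**What the plan says.** **Timing.** Under Data From Routinely Conducted Assessments and Clinical Records, blood tests, medication, body mass, vital parameters and cycle ergometry "will be recorded 3 times (at week –3 to –2, time point 0, and week 10"). The next sentence reads "Adverse event reporting will take place at week 10". No other part of the text gives a time for adverse events.

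**Exposure and follow-up.** In the study procedures textbox, under week −1, "participants allocated to the intervention group receive the aktivplan physical activity planning session before discharge from the phase II rehabilitation program". After that, "patients in both study groups are followed up for 10 weeks after discharge from phase II rehabilitation".

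**Definition.** The secondary outcomes list has "Patient safety (adverse events reporting according to regulatory standards: number, type, and severity of adverse events").

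**Aim.** The Aim section says that clinical outcomes are collected, among other things, "to demonstrate the patient safety of the intervention". The Outcomes section words the same purpose as "to provide evidence toward demonstrating patient safety of the intervention". The abstract's objective speaks only of collecting clinical and safety outcomes.

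**Discontinuation.** The end of the Qualitative Interview section says that participants who stop or deviate from the intervention will be encouraged to complete all assessments. It does not mention those who withdraw from the study.

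**The concern.** There are two linked problems.

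First, a safety count tied to the final visit depends on who attends it. An adverse event is a plausible reason to leave a study of self-directed exercise. If events make withdrawal more likely, the participants without a week-10 visit are those with more events, and the count is biased downward. Drop-out is itself a primary outcome of this pilot, so some is foreseen.

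The planned handling of missing data does not repair this. The sensitivity analysis in the Analyses section takes minima and maxima from complete cases. If no completer has an event, both are zero, and the worst case still gives withdrawn participants no events.

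Second, the Aim section promises a conclusion that the number of exposed patients cannot carry. A low or zero count could then be given more weight than it deserves in the planned paper on preliminary clinical outcomes.

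**Working it through.** **Inputs from the article**
- Planned size: "Forty patients undergoing phase II rehabilitation will be recruited from 2 study sites (20 patients per site").
- Recruited: 34 (Results).
- Detectable prevalence: 7.5% with 95% confidence at N = 40 (Sample Size).

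**Assumptions, because the article gives no figure**
- Allocation 1:1, hence about 20 exposed as planned and 17 as recruited.
- Unascertained withdrawal of 20% or 30%, for illustration.
- Event risk in withdrawn participants equal to, or twice, that of the others.

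**Step 1: reproduce the plan's own figure.** To see at least one event of prevalence p with 95% confidence, n = ln(0.05)/ln(1 − p). For p = 0.075 this is 38.4, so 39 patients. With 40 patients the probability is 1 − 0.925^40 = 95.6%, and the smallest detectable prevalence is 1 − 0.05^(1/40) = 7.2%. The stated figure is sound for both arms together.

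**Step 2: apply the same reasoning to the exposed arm.** Detectable prevalence is 1 − 0.05^(1/n). With zero events, the exact two-sided 95% upper limit is 1 − 0.025^(1/n). The chance of seeing at least one event at a true 7.5% rate is 1 − 0.925^n.

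| Exposed n | Basis | Detectable prevalence | Upper limit at 0 events | Chance of ≥1 event at 7.5% |
|---|---|---|---|---|
| 20 | half of 40 | 13.9% | 16.8% | 79% |
| 17 | half of 34 | 16.2% | 19.5% | 73% |
| 15 | 25% of 20 without week-10 data (assumed) | 18.1% | 21.8% | 69% |

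**Step 3: share of events missed.** If a fraction d withdraws unascertained, with risk RR times that of the others, the share missed is d·RR / [(1 − d) + d·RR]. The base risk cancels.
- d = 0.20, RR = 1: 0.20/1.00 = 20%.
- d = 0.20, RR = 2: 0.40/1.20 = 33%.
- d = 0.30, RR = 1: 0.30/1.00 = 30%.
- d = 0.30, RR = 2: 0.60/1.30 = 46%.

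**Step 4: length of the period.** From the week −1 planning session to week 10 is about 11 weeks of exposure, for which one reporting time is stated.

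**The case against.** The strongest reply is that a condensed sentence in a journal article is being read too literally. A reader might infer three things that the documents do not support.

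- **That events are gathered by patient recall over about 11 weeks.** The article names no look-back window and does not say that recall is the source. The sentence stands under a heading that includes clinical records, so a week-10 report may draw on them.
- **That nothing is asked at discharge.** The schedule in Figure 2 is not shown, and adverse event procedures are commonly left to the full protocol. In week −1 participants are still in rehabilitation, where staff can note events. The article also cites Good Clinical Practice and the EU Medical Device Regulation, and describes monitoring visits.
- **That everyone who drops out contributes no safety data.** Those who stop the intervention are encouraged to complete all assessments. Someone who stops because of an event may therefore still be followed up.

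Nor does the article claim throughout to demonstrate safety. The Outcomes section and the abstract are softer, and the Analyses section rules out confirmatory inference and already plans 95% CIs for the secondary clinical outcomes.

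These replies limit the point without removing it. The article does not merely omit the timing. It states one, next to measures with three, and says nothing on full study withdrawals. Regulatory standards may well cover the gap, but the two statements have to be joined for a reader to know. The softer wording elsewhere makes the Aim section inconsistent as well as too strong.

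**Conclusion.** The point holds in a limited form. As written, week 10 is the only stated time for adverse event reporting, and no route is described for participants who withdraw from the study. Their events may be missed; the text does not establish that they are.

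The possible undercount is 20% to 33% at 20% unascertained withdrawal and 30% to 46% at 30%, for equal to doubled risk. All of these rates and risks are assumptions.

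The wording problem does not depend on drop-out. With about half of 40 or of 34 patients exposed, zero events would still be compatible with a true rate of up to 16.8% or 19.5%, under an allocation ratio that the article does not state. That cannot demonstrate safety. It can describe what was seen, which is close to what the Outcomes section already says.

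**What to change.** **For this trial.** Data collection ended in August 2024, so no contacts can be added. What remains possible:
- State the period that the week-10 report covers and its source, and reconcile the week-10 timing with the reference to regulatory standards in the secondary outcomes.
- Check clinical records for withdrawn participants, where consent allows.
- Report events by arm, with the number actually ascertained as denominator and exact (Clopper-Pearson) intervals. This refines the CIs already planned.
- Reword the Aim section so that it speaks of describing adverse events, in line with the Outcomes section, and give the upper confidence limit with the result.

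**For the definitive trial.** Record adverse events with the same prompt in both arms at time point 0, at any withdrawal and at week 10. The same prompt matters because assessors are unblinded and in-app messaging gives the intervention arm a contact channel that controls lack. Discharge and week 10 are existing visits. A withdrawal contact would be new, since the article describes none and participants may leave without giving a reason.

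**Cost.** A few minutes per contact, a record check for a few withdrawals, some rewording, and a less favourable safety statement.

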#### Self-Reported Questionnaires

At week –3 to –2, time point 0, and week 10, study participants in the intervention and control groups will complete questionnaires on kinesiophobia (selected items from the Tampa Scale of Kinesiophobia [32]), exercise self-efficacy (Exercise Self-Efficacy Scale [33]), depression and anxiety (Patient Health Questionnaire-4 [34]), and health-related quality of life (EQ-5D-5L [35]). At week −3 to −2, they will complete a personality questionnaire (Big Five Inventory [36]) and the Affinity for Technology Interaction questionnaire [37]. At week −3 to −2 and at week 10, they will complete the Rapid Assessment of Physical Activity questionnaire [38]. At week 10, they will complete the International Physical Activity Questionnaire [39] and a questionnaire rating the comfort of the wearable sensor devices (Comfort Rating Scale [40]).

At week 10, study participants in the intervention group will complete questionnaires on the usability and user experience of the aktivplan app, including the mHealth App Usability Questionnaire [41], the Unified Theory of Acceptance and Use of Technology 2 questionnaire [42], the Mobile App Rating Scale [43], and the AttrakDiff mini questionnaire [44]. For some of these questionnaires, only selected relevant sections are used.

#### aktivplan Use Tracking

During the 10-week intervention period, use of the aktivplan app will be automatically tracked, including participants’ log-in and duration, planned physical activity sessions that have been marked as completed by participants, and additional physical activity sessions that participants enter into the app. Adherence will be quantified as a percentage of planned physical activity sessions that have been marked as completed by participants. Engagement with the app will be quantified by the time spent interacting with the app. Notably, longer duration of interaction with the app does not necessarily equate to meaningful engagement in the sense of adherence to the personal physical activity plan.

#### Physical Activity and Heart Rate Measurements

Participants’ physical activity and heart rate will be measured during the last 3 weeks of the study (weeks 8-10) in both study groups, using 2 wearable sensor devices (wearables). Study participants will be instructed to wear the devices daily for 3 weeks during waking hours, and to return the wearables at the final study visit (10-week follow-up). Physical activity will be measured with the ActiGraph GT9X Link accelerometer (ActiGraph LLC), worn on the nondominant wrist. Heart rate will be measured with the Polar Verity Sense device (Polar Electro Oy), worn on the nondominant upper arm or forearm. Study participants will receive both devices by post, together with written instructions and a link to an online instructional video on how to operate the wearables. Telephone support will be provided by the study team if needed.

#### Qualitative Interview

At week 10, audio-recorded semistructured interviews will be conducted in both study groups to inquire about participants’ experiences of participating in the study and any self-initiated support for physical activity during the study period. Participants in the intervention groups will also be asked about their experiences of using the aktivplan app. The interview schedule is provided in Multimedia Appendix 4.

Study participants who discontinue or deviate from the intervention protocol will be encouraged to complete all outcome assessments regardless.

### Data Collection From Health Care Professionals

#### Overview

To assess usability, user experience, and acceptance of the aktivplan app from the perspective of health care professionals, data will be collected from those members of staff at the study sites who implement the aktivplan digital health intervention with patients. These members of staff are physiotherapists or sports scientists who have provided written informed consent to have their data collected and who have received a full day of training on the aktivplan digital health intervention before the start of the study.

#### Self-Reported Questionnaires

At the beginning of the study, the health care professionals will complete the Affinity for Technology Interaction and Big Five Inventory questionnaires and rate their self-efficacy for implementing the aktivplan intervention. During the running of the study, the health care professionals will keep concurrent reflective notes on the use of the intervention, document any technical difficulties, and log their time requirements for implementing the intervention. After each aktivplan physical activity planning session, the 9-item Shared Decision Making Questionnaire [45] and items from the Nasa-Task Load Index [46] will be completed. At the end of the study, the health care professionals will again rate their self-efficacy for implementing the aktivplan intervention, and complete the mHealth App Usability Questionnaire, Mobile App Rating Scale, Unified Theory of Acceptance and Use of Technology 2, AttrakDiff mini, and the Normalization Measure Development [47] questionnaires.

#### Qualitative Focus Group

At the end of the study, a focus group discussion will elicit the health care professionals’ views on implementing the aktivplan intervention in routine clinical practice at the study sites, facilitating and hindering factors for the implementation of aktivplan, any problems experienced with the app, suggestions for improvement and new desired features of the app, and any problems and other observations regarding the conduct of the study that would need to be considered in the design of a larger definitive trial. The focus group will be audio and videorecorded and moderated by 2 researchers. The topic guide is given in Multimedia Appendix 5.

### Outcomes

The primary outcomes address the primary study aim, that is, to pilot and assess the feasibility of a future randomized controlled trial design to investigate the effectiveness of the aktivplan digital health intervention; and to assess the usability, user experience, and acceptance of the aktivplan app. The primary outcomes are presented in Textbox 3.

The secondary outcomes address the secondary study aim, that is, the collection of clinical outcomes to inform the sample size calculation for a future definitive effectiveness trial and to provide evidence toward demonstrating patient safety of the intervention. The secondary outcomes are presented in Textbox 4.

Primary outcomes.Recruitment rate (number of recruits per week, percentage of screened patients who were recruited, and percentage of eligible patients who were recruited)Drop-out rate (number of drop-outs at the 10-week follow-up and percentage of recruited patients who dropped out)Data completeness (percentage of missing data fields in study database)Adherence to the aktivplan digital health intervention (automated use logging of the aktivplan app and video recording of the aktivplan physical activity planning session)Usability of the aktivplan app (mHealth App Usability Questionnaire)User experience of the aktivplan app (AttrakDiff mini questionnaire)User acceptance of the aktivplan app (Mobile App Rating Scale and Unified Theory of Acceptance and Use of Technology 2)Technical reliability of the aktivplan app (number and types of technical problems and qualitative data)Use of alternative and additional strategies for supporting physical activity (number and types of additional strategies and qualitative data)Experiences and perspectives of rehabilitation professionals regarding the intervention and study procedures (qualitative data from focus groups)

Secondary outcomes.Exercise capacity (highest mechanical power output achieved during incremental cycle ergometry, peak power)Physical activity behavior (accelerometry and daily minutes of moderate to vigorous physical activity)Body massArterial blood pressureBlood cholesterol levelsGlycated hemoglobin levelsSmoking (number and type of smoking products per week)Health-related quality of life (EQ-5D-5L questionnaire)Exercise self-efficacy (Exercise Self-Efficacy Scale)Depression and anxiety (Patient Health Questionnaire-4)Kinesiophobia (selected items from the Tampa Scale of Kinesiophobia)Patient safety (adverse events reporting according to regulatory standards: number, type, and severity of adverse events)

### Data Management

At the study sites, data will be recorded on paper-based case report forms (CRFs). Following completion of data collection, the CRFs and electronic data collection devices (wearables, dictaphones, and video cameras) will be collated and securely stored at the study sponsor site. Data from CRFs will be entered onto a Microsoft Excel file. Quality of data entry will be assessed by independently cross-checking the accuracy of 10% of data cells. After completion of the analysis, study data will be securely archived by the sponsor for 10 years.

